**Table 10: Maximum numbers of patients per comparison group for approximately 90% power, 5% 2-sided significance overall**

| Efficacy (%) (E) | Incidence /100py | n events observed in control arm for interim analysis | N participants per group | Assuming 10% loss of PY |
|------------------|------------------|-------------------------------------------------------|--------------------------|-------------------------|
| 50               | 3.0              | 18                                                    | 919                      | 1021                    |
|                  | 4.0              | 18                                                    | 805                      | 894                     |
|                  | 5.0              | 18                                                    | 713                      | 792                     |
| 70               | 3.0              | 7                                                     | 561                      | 623                     |
|                  | 4.0              | 7                                                     | 500                      | 556                     |
|                  | 5.0              | 7                                                     | 434                      | 482                     |
| 80               | 3.0              | 4                                                     | 461                      | 512                     |
|                  | 4.0              | 4                                                     | 399                      | 443                     |
|                  | 5.0              | 4                                                     | 357                      | 397                     |

### 9.3.2 PREP COMPARISON

The PrEP study aims to show the effectiveness of TAF/FTC is not unacceptably lower than the effectiveness of TDF/FTC, assessed from the observed lower confidence limit for the Averted Infections Ratio (AIR). Table 11 shows the probability (power) that the 5% lower confidence limit for the AIR will exceed either 50%, 60%, or 70% as a function of (a) the effectiveness of TDF/FTC, and (b) the hypothetical placebo incidence. The calculations assume (a) that TAF/FTC and TDF/FTC are equally effective (the standard assumption in PrEP non-inferiority trials), and (b) 10% loss of PYRS follow-up (as in Section 9.3.1.).

**Table 11: Probability (%) that lower 5% confidence limit for AIR exceeds certain critical non-inferiority margins**

| Non-inferiority margin (%) | Effectiveness (%) of TDF/FTC | Placebo incidence (per 100 PY) |     |     |
|----------------------------|------------------------------|--------------------------------|-----|-----|
|                            |                              | 3.0                            | 4.0 | 5.0 |
| 50                         | 50                           | 31                             | 38  | 44  |
| 50                         | 60                           | 47                             | 56  | 64  |
| 50                         | 70                           | 68                             | 78  | 86  |
| 50                         | 80                           | 90                             | 96  | 98  |
| 60                         | 50                           | 22                             | 26  | 30  |
| 60                         | 60                           | 31                             | 38  | 44  |
| 60                         | 70                           | 46                             | 56  | 64  |
| 60                         | 80                           | 70                             | 80  | 88  |
| 70                         | 50                           | 15                             | 17  | 19  |
| 70                         | 60                           | 20                             | 24  | 27  |
| 70                         | 70                           | 29                             | 35  | 40  |
| 70                         | 80                           | 45                             | 54  | 62  |

**Table 11** shows there is reasonable power of showing at least 50% preservation of effect provided that TDF/FTC effectiveness is at least 70%, underlining the importance of optimising adherence to PrEP. Demonstrating at least 60% preservation of effect is more challenging, while demonstrating at least 70% preservation of effect is very unlikely.

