| Number of Participants to be Studied | 
The vaccine component of the trial requires a minimum of 1668 eligible individuals to support the final analysis. They will be drawn from key populations attached to one of the participating clinical research centres (see Section 3.3 for more details).
                                                                                                                                                                                                                                                                                                                                                                                                                                                                                                                                                                                                                                                                                                                                                                                                                                                                                                                                               |

| SUMMARY INFORMATION TYPE         | SUMMARY DETAILS                                                                                                                                                                                                                                                                                                                                                                                                                                                                                                                                                                                                                                                                                                                                                                                           |

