### 4.2 RANDOMISATION CODES & UNBLINDING

Randomisation codes and unblinding are considered in [Section 5.6](#).

Study staff and participants will not know who has been allocated vaccine and who has been allocated placebo, but it is not possible to blind staff to the difference in volume as they will be administering 1ml in one arm and 0.45ml in the other at the same timepoint on four occasions (see section 5.3.6). Study staff will therefore be able to identify who has been randomised to the schedule that includes gp140 in MLPA-L or its matched placebo.

Allocation to the vaccine regimens will be in the ratio of 1:1:1 for groups A:B:C respectively. As the volume of the recombinant proteins differs between the two active arms, the placebo injection will be further divided 1:1 to 1ml: 0.45ml in order to ensure that staff administering the injection cannot differentiate between active and placebo.

As the trial is adaptive, the ratio may change to 1:1 during the trial if one of the vaccine regimens is discontinued or temporarily paused due to an issue with one of the products. If this is necessary, a new randomisation database will be implemented with the new list and the previous database archived after completing the quality checks.

The pharmacist at each centre will know the precise allocation throughout the trial as they will have a list that is mapped to each randomisation list

The randomisation to control PrEP:experimental PrEP is 1:1 and all study staff and participants will know the allocation after randomisation as this is open-label.

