## **9.2.2 PREP TRIAL:**

### **9.2.2.A Primary**

- ▶ HIV acquisition at or before visit 9 by a participant who was HIV negative at enrolment
- ▶ A clinical decision to discontinue the PrEP regimen for an adverse event that is considered related to product

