### 9.5.2 PREP STUDY ANALYSES

The primary analysis will be mITT i.e. including all randomised participants but excluding those found to be HIV positive at enrolment. The incidence rate of new HIV infections, up to and including visit 9, will be computed for each randomised arm. The two rates will be directly compared using the rate difference and the rate ratio, and confidence intervals derived using the Poisson distribution. In addition, the Averted Infections Ratio (AIR) will be calculated based on: (a) an estimate of the hypothetical placebo incidence from the registration cohort (b) an estimate of the hypothetical placebo incidence based on follow-up of trial participants after visit 9 (c) the estimated effectiveness of TDF/FTC based on adherence data (d) a synthesis of (a), (b), and (c). The lower 5% confidence limit will provide a lower bound estimate of the proportion of infections averted by TAF/FTC relative to TDF/FTC. No formal significance tests of non-inferiority will be conducted since the definition of the non-inferiority margin is largely arbitrary.

If there are sufficient HIV endpoints, an analysis stratified by gender will also be conducted.

If it transpires that neither vaccine arm confers any protection, then the effect of vaccination can be ignored in the PrEP analysis. However, if some level of protection is demonstrated then statistical models will be developed to model jointly the effects of PrEP and the vaccine regimens. This is

pertinent to the calculation of the AIR since the estimate of the hypothetical placebo incidence from the registration cohort would be biased upwards.

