## 11.2 ETHICAL CONDUCT

### 11.2.1 ETHICAL CONSIDERATIONS

PrEPVacc is assessing interventions to reduce the risk of HIV acquisition and therefore sites will be recruiting individuals at risk of acquiring HIV. Populations at risk of HIV are frequently vulnerable because of the intersecting social syndemics of poverty, violence, drug and alcohol addiction, and depression. In PrEPVacc participants will be provided with condoms and PrEP, both of which are known to prevent HIV, but the study supply of PrEP will cease once they have completed three injections plus two weeks follow-up. Study staff will inform participants where they can access PrEP locally and support them to do so where this is possible, and continue to supply condoms. Please see section 1.5 for context and rationale.

The vaccines are not licensed and some have only been administered to a few hundred individuals so there may be adverse events that we have not anticipated.

Participants who receive active vaccine may develop antibodies that lead to a positive point of care HIV test in future, including after the trial has finished. Study staff will provide participants with an identity card verifying their participation in a HIV vaccine trial and continued access to laboratory testing and certification of status.

The materials to support informed consent will be developed to ensure that participants understand the risks and benefits of participation, in particular that the design includes a placebo vaccine, that no-one knows whether the active vaccines can reduce the risk of HIV, that they may require additional tests after the study to distinguish between a vaccine reaction and HIV infection, and that study will only supply PrEP for 26 weeks. The materials developed will take account of the level of literacy in each centre. Participants who are not able to read will be asked to provide their thumbprint. They will be accompanied by a witness of their choice who can read and who will be asked to sign the consent form.

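### The Table 11 power for showing 50% preservation is too high at 70% and 80% TDF/FTC effectiveness, because a large-sample formula is applied to about 2 to 6 expected infections per arm

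*Protocol*

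**What the plan says.** Protocol section 9.3.2 judges TAF/FTC against TDF/FTC by the lower 5% confidence limit of the AIR. Table 11 gives the probability that this limit exceeds 50, 60 or 70%. "The calculations assume (a) that TAF/FTC and TDF/FTC are equally effective", and they allow for "10% loss of PYRS follow-up". For the 50% margin at placebo incidence 3/4/5 per 100 PY, the table states 68/78/86% when TDF/FTC is 70% effective and 90/96/98% when it is 80% effective.

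The text under the table draws the conclusion that "there is reasonable power of showing at least 50% preservation of effect provided that TDF/FTC effectiveness is at least 70" percent. It is more cautious about the 60% and 70% margins.

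On the analysis, section 9.5.2 says: "The lower 5% confidence limit will provide a lower bound estimate of the proportion of infections averted by TAF/FTC relative to TDF/FTC". It takes the hypothetical placebo incidence from several estimated sources and plans no formal non-inferiority test. The protocol does not give the power formula, the expected number of infections or the interval method for the AIR.

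**The concern.** The PrEP endpoint is "HIV acquisition at or before visit 9 by a participant who was HIV negative at enrolment", a window of about half a year. With effective PrEP in both arms, very few infections are expected in that time. A power formula that treats the log AIR as normal with a fixed standard error need not be accurate at such counts, and a limit built the same way may not have its nominal error rate.

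Table 11 is the only quantitative support given for the PrEP comparison. If its figures are too high, investigators, funders and the data monitoring committee are told that the trial will probably show 50% preservation when, at the effectiveness the sentence itself names, the chance may be little better than even. The protocol's summary lets that committee recommend randomising more participants to the PrEP component alone, so the planning figures can affect a real decision.

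**Working it through.** **Inputs**

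- Sample size: the vaccine component "requires a minimum of 1668 eligible individuals to support the final analysis" (Summary of Trial).
- Allocation: "The randomisation to control PrEP:experimental PrEP is 1:1" (section 4.2), so 1668 / 2 = 834 per arm.
- Duration: "study will only supply PrEP for 26 weeks" (section 11.2.1), taken as 0.5 year.
- Loss: 10% of person-years (section 9.3.2).
- Person-years per arm: 834 × 0.5 × 0.9 = 375.3.
- Limit: one-sided 5%, z = 1.645. True AIR = 1 (equal effectiveness).

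**Reproducing Table 11**

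Let L = placebo incidence × 375.3 and μ = L × (1 − effectiveness), the expected infections per arm. Then

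power = Φ( −ln(margin) / SE − 1.645 ), with SE = √(2μ) / (L − μ).

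Example with 50% margin, 70% effectiveness and 4 per 100 PY: L = 0.04 × 375.3 = 15.01; μ = 0.3 × 15.01 = 4.50; SE = √9.01 / 10.51 = 0.2856; 0.6931 / 0.2856 − 1.645 = 0.782; Φ(0.782) = 78.3%. The table states 78%.

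All 36 cells are reproduced within 0.5 points. Alternatives fit worse: a 2.5% limit is off by up to 12.8 points, a linear contrast by up to 7.2, no loss of person-years by up to 4.4, and 24 weeks by up to 3.4. The formula is therefore inferred, but the match is close.

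**Expected infections per arm (3/4/5 per 100 PY)**

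- 70% effectiveness: 3.38 / 4.50 / 5.63
- 80% effectiveness: 2.25 / 3.00 / 3.75

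**Exact check**

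I enumerated independent Poisson counts x (TAF/FTC) and y (TDF/FTC), with L known, and summed the probability of outcomes in which the lower limit exceeds 50%. The log-Wald limit is ln[(L − x)/(L − y)] − 1.645 √[x/(L − x)² + y/(L − y)²]. The likelihood-ratio and score limits test AIR = 0.5 with the TDF/FTC rate at its constrained maximum-likelihood value. True error is the same sum with AIR set to 0.5.

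| 50% margin, 3/4/5 per 100 PY | 70% effective | 80% effective | True error (nominal 5%) |
|---|---|---|---|
| Stated in Table 11 | 68/78/86 | 90/96/98 | – |
| Log-Wald | 64/75/80 | 83/91/94 | about 10–11% at 70%, 10.5–12% at 80% |
| Likelihood ratio | 51/61/68 | 69/80/87 | 5.4–6.3% |
| Score | 40/52/64 | 60/70/84 | 3.6–4.4% |

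The shortfall is 3 to 7 points with log-Wald and 11 to 21 points with likelihood ratio. Log-Wald comes closest to the stated power only because its error is about twice nominal.

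**Placebo rate estimated**

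The protocol does not give the person-years behind the placebo estimate, so I assumed 250 to 1380. At 70% effectiveness and 4 per 100 PY, log-Wald power falls from 75% to 72% (1380 PY), 71% (1000 PY), 68% (500 PY) and about 63 to 64% (250 PY). With the likelihood-ratio limit and 1000 PY, power is 46/55/64% at 70% effectiveness and 63/74/82% at 80%.

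**The case against.** Several counter-arguments have force.

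- **The arithmetic is sound.** Every cell follows from a standard delta-method formula. That is so; the fault is using the formula at these counts.
- **The interval method may be left to the SAP.** This is also fair, and the size of the shortfall depends on it. But the stated figures are too high under every limit tried, and the power sentence is the protocol's own.
- **No formal test depends on the table.** Section 9.5.2 plans none, and the minimum of 1668 comes from the vaccine comparison. This limits the consequences. Section 9.3.2 still makes the lower AIR limit the means of showing the PrEP result.
- **375 PY is a minimum.** Dropouts before the third injection are replaced, up to 620 per vaccine group, and visit 9 can fall near week 33 within the upper targets of Table 1 (7 + 22 + 4). An upper illustration is 930 × 33/52 × 0.9 = 531 PY per arm. Likelihood-ratio power is then 63/74/82% at 70% effectiveness and 82/91/95% at 80%. That is better, but the Table 11 formula at 531 PY would give 80/89/94% at 70%, so the approximation would still overstate. The published table is in any case computed at 375 PY.

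A reader might infer two stronger points that the document does not support. The first is that Table 11 treats the placebo incidence as known. At true AIR = 1 the first-order placebo term, proportional to (1/(λP − λE) − 1/(λP − λC))², is zero, so the formula gives the same table either way. The second is that all of Table 11 is overstated. With a log-Wald limit, exact power at the 60% margin and 70% effectiveness is 48/55/64% against 46/56/64% stated. At the 70% margin it is 31/37/43% against 29/35/40% (70% effectiveness) and 52/57/65% against 45/54/62% (80%).

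**Conclusion.** The point holds for the six cells on which the power sentence rests. At the effectiveness the sentence names, a limit close to its 5% level (likelihood ratio) gives 51 to 68% power where the table states 68 to 86%. At 80% effectiveness the conclusion survives in part: about 80% or more at incidence of 4 per 100 PY or higher, but 69% at 3 per 100 PY.

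These figures assume 1668 randomised, 0.5 year each, 10% loss, Poisson counts, equal effectiveness and a known placebo rate. A score limit gives lower power. Estimating the placebo rate lowers it further, by an amount that depends on person-years the protocol does not state. More participants or longer time to visit 9 would raise it. The formula match and the low counts are firm; the exact size depends on the interval chosen.

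**What to change.** 1. Print the expected infections per arm beside Table 11.
2. Recompute the table by Poisson enumeration or simulation, with a lower limit that holds close to 5% (likelihood ratio, for example) and the placebo rate estimated as section 9.5.2 plans. State the person-years assumed for that estimate.
3. Use the same limit for the AIR in the analysis, in the protocol or the SAP.
4. Reword the conclusion. With a likelihood-ratio limit and known placebo rate it would read: at the minimum sample size, power to show 50% preservation is about 50 to 70% if TDF/FTC is 70% effective, and reaches about 80% or more if it is 80% effective and placebo incidence is at least 4 per 100 PY. Lower these figures if the recomputation with an estimated placebo rate requires it.

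The cost is a short calculation and a wording change. The stated power becomes less favourable; recruitment and trial conduct do not change.

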## 9.4 INTERIM MONITORING & ANALYSES

An IDMC Charter will be drawn up that describes the membership of the IDMC, relationships with other committees, terms of reference, decision-making processes, and the timing and frequency of interim analyses (with a description of stopping rules and/or guidelines, if any).

The IDMC will regularly review safety data and incident HIV data by randomised arm as described in the charter (for both randomisations).

In addition for the vaccine trial, there is one formal planned interim analyses to be performed when approximately 7 HIV incident cases are observed in the control arm. Recommendation for possible discontinuation of further enrolments and vaccines for those already enrolled to intervention arm(s) will be made from the results of this analysis.

## 9.5 ANALYSIS PLAN (BRIEF)

The analyses will be described in detail in a full SAP. This section summarises the main issues.

### 9.5.1 VACCINE TRIAL EFFICACY ANALYSES

For the Primary efficacy endpoint analysis, a modified intent-to-treat (mITT) approach will be adopted whereby participants randomised but later found to be HIV positive at or before the timepoint 2 weeks after the third immunisation will be excluded from the primary analysis.

A time-to event analysis will be adopted to estimate a hazard ratio for each pairwise comparisons (i.e. each active vaccine arm against placebo). Participants who are lost to follow-up will contribute person-years up to their last clinical follow-up. HIV incidence rates will be calculated for each allocation and the effect on HIV incidence will be determined using Cox Proportional Hazards models adjusting for site. Product efficacy will be expressed as 1 minus the hazard ratio for each active vaccine arm when compared to placebo.

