|                                             | 
 
▶ Other clinical and laboratory adverse events
 
 
Secondary Immunological Outcomes:
 
 
▶ Binding antibodies to CN54gp140 and AIDSVAX® B/E gp120
 
 
PrEP analysis:
 
Secondary Safety Outcomes
 
 
▶ An adverse event leading to a clinical decision to discontinue or interrupt the product schedule, regardless of relationship
 
▶ Serious adverse events
 
▶ Genotypic resistance at HIV seroconversion, focussing on the mutations selected by tenofovir and emtricitabine (codons 65, 70, 184 in reverse transcriptase)
 
 
Secondary Adherence Outcomes:
 
 
▶ Adherence assessed by (a) self-report (b) results of point of care urine tests (c) TFV DP levels measured on dry blood spots (DBS) in red blood cells (d) total number of pills dispensed
 
 
Specimens will be collected as per Table 1 and processed for secondary analyses or stored for future exploratory analyses, subject to funding (see Section 9.2.1.C).
 |
| Randomisation                        | 
Participants will be randomised at each clinical centre through web randomisation after entering the eligibility criteria. Randomisation will be stratified by centre and by gender for vaccines and PrEP.
 
Clinic staff and participants will be blind to allocation of active or placebo vaccines, but the pharmacist preparing the vaccines will know.
 
As the volume of CN54gp140 in MPLA-L is 0.45ml and given at the same timepoints as products with a volume of 1ml, clinic staff will be able to identify participants allocated to this CN54gp140 in MPLA-L or matched placebo.
 
Clinic staff and participants will know which PrEP agent each participant is allocated to.
                                                                                                                                                                                                                                                                                                                                                                                                                                                                                                                    |

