### ***Rationale for the evaluation of TAF/FTC as PrEP***

TDF/FTC is very safe, but renal and bone toxicity are concerns with long term use, especially as individuals age and acquire co-morbidities that could aggravate these toxicities. TAF/FTC requires a

smaller concentration of tenofovir than TDF/FTC with two advantages: reduced toxicity and reduced manufacturing costs. In light of the reduced costs, it is likely that TAF/FTC will replace TDF/FTC in settings where generic drugs are used. The DISCOVER trial compared TAF/FTC to TDF/FTC in MSM and transgender women in North and South America and Europe observing only 7 infections in the 2,694 TAF/FTC participants compared to 15 in the 2,693 TDF/FTC participants. Although regulatory authorities may feel able to extrapolate the results to heterosexual men, this is unlikely to be the case for women due to the differences in tissue penetration. The lack of clinical effectiveness data for TAF/FTC when used as PrEP in heterosexual populations, particularly women, could be a critical gap if TAF/FTC replaced TDF/FTC as the main drug in Sub-Saharan Africa and other settings where the dominant transmission route is heterosexual sex.

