We have chosen to evaluate vaccines and PrEP in a way that a national HIV vaccine programme would be likely to combine the two with daily study PrEP to support the time to peak immune responses and thereafter available to all who wish to continue. We recognise the potential for a conflict of interest for staff when promoting PrEP in a vaccine trial and hope including PrEP as a study drug will address this, and that uptake and adherence will be higher as a consequence, potentially overcoming misgivings that participants may have had about taking PrEP when they enrolled. The data gathered in the preceding Registration Cohort has assisted in mobilising PrEP services, and therefore it is anticipated that investigators will be able to support participants motivated to continue PrEP after they complete the first three immunisations through access in the community or direct provision to a sustainable supply. The Registration Cohort has confirmed that new HIV infections occur even when PrEP is available, particularly in female participants, underscoring the need for other interventions to prevent HIV.

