## 9 STATISTICAL CONSIDERATIONS

### 9.1 METHOD OF RANDOMISATION

There are two separate randomisations applied concurrently in PrEPVacc:

For the vaccine part of the trial participants will be randomised 1:1:1 to either

- ▶ A: DNA-HIV-PT123 and AIDSVAX® B/E (target wks 0,4,24,48)
- ▶ B: DNA-HIV-PT123 and CN54gp140+MPLA-L (target wks 0,4), then MVA-CMDR and CN54gp140+MPLA-L (target wks 24,48)
- ▶ C: Saline placebo (target wks 0,4,24,48)

For the PrEP part of the trial participants will be randomised 1:1 to either

- ▶ A: TDF/FTC once daily from week 0 until visit 9 (CONTROL)
- ▶ B: TAF/FTC once daily from week 0 until visit 9 (EXPERIMENTAL)

Both randomisations will be stratified by centre and gender using a web-based system controlled through an authorised user name and password, at each site. Before each allocation, the participant's eligibility will be confirmed and the stratification factor entered into the database. Randomisation lists for both randomisations will be generated by an independent statistician not involved in the day to day running of the study.

In the event the ratio need to change to 1:1 during the trial, a second randomisation list will be implemented and the first randomisation database archived (see [Section 4.2](#)). A third list will be prepared in order to be ready for a return to 1:1:1.

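### Gender stratifies both randomisations but is absent from the vaccine Cox model, and the only PrEP analysis by gender is conditional on an unstated number of infections

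*Protocol*

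**What the plan says.** On allocation, section 9.1 states: "Both randomisations will be stratified by centre and gender using a web-based system". The Summary of Trial agrees: "Randomisation will be stratified by centre and by gender for vaccines and PrEP".

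On the vaccine analysis, section 9.5.1 specifies a time-to-event comparison of each active arm with placebo, in which "the effect on HIV incidence will be determined using Cox Proportional Hazards models adjusting for site". Gender is not named, and section 9.5.1 describes no analysis by gender.

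On the PrEP analysis, section 9.5.2 includes everyone randomised except those found HIV positive at enrolment, and says: "The two rates will be directly compared using the rate difference and the rate ratio, and confidence intervals derived using the Poisson distribution". It then describes the AIR. Neither stratification factor is named for the rates or the AIR. Gender enters once: "If there are sufficient HIV endpoints, an analysis stratified by gender will also be conducted". No threshold is given.

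On why women matter, section 1.5.2 gives this reason for the PrEP comparison: "The lack of clinical effectiveness data for TAF/FTC when used as PrEP in heterosexual populations, particularly women, could be a critical gap". The same section reports from the Registration Cohort that "new HIV infections occur even when PrEP is available, particularly in female participants".

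Section 9.5 is headed as a brief plan and leaves detail to a separate statistical analysis plan.

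**The concern.** There are two separate points.

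- **Vaccine model.** An analysis should normally reflect the factors used to restrict the randomisation. The protocol is not silent here: it names one adjustment and leaves out the other stratification factor. Section 1.5.2 itself suggests that gender is prognostic for infection.
- **PrEP results in women.** The protocol argues that regulators are unlikely to extrapolate existing TAF/FTC results to women, yet the result in women is the one that the plan allows to be omitted. With no stated threshold, the decision on whether there are enough infections would be taken once the counts are known. The wording also leaves open whether the analysis is a gender-adjusted overall estimate or separate results for women and men.

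What is at stake is modest for the vaccine and larger for PrEP: whether a prespecified result in women appears at all.

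**Working it through.** **1. The protocol's own sample size.** Table 10 gives 500 per group for 70% efficacy and 4 infections per 100 person-years.

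- Inflation for 10% loss: 500 / (1 - 0.10) = 555.6, that is 556.
- Three groups: 3 x 556 = 1668. Both figures match section 9.3.1.
- The 500 comes from the nstage software. Its stage-wise error rates, accrual and follow-up are not given, so it cannot be re-derived.

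**2. Effect of leaving gender out of the vaccine model.** One active-versus-placebo comparison was simulated with allocation stratified by gender, 500 per arm and 4 per 100 person-years overall. Assumed, because the protocol does not state them: 1.5 years of follow-up, 50-80% women, and a female-to-male incidence ratio of 1 to 4. There were 20,000 replicates under the null and 10,000 at a hazard ratio of 0.30.

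| | Gender omitted | Gender included |
|---|---|---|
| Type I error (nominal 5%) | 4.7-5.1% | 4.8-5.1% |
| Power at hazard ratio 0.30 | 92.7-93.8% | 92.9-93.9% |
| Mean estimated hazard ratio | 0.286-0.289 | 0.285-0.288 |

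The gain in power is at most about 0.2 points. Omission is very slightly conservative. The 556 per group does not change.

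**3. Could selection after randomisation produce bias?** The vaccine endpoint requires three completed immunisations (section 9.2.1.A), and pregnancy stops injections (section 5.7). Take an assumed scenario with no vaccine effect: 60% women, incidence 5 per 100 in women and 2 in men, 3% of men excluded in each arm, and 15% of women excluded on active against 5% on placebo.

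- Active: (0.60 x 0.85 x 5 + 0.40 x 0.97 x 2) / (0.60 x 0.85 + 0.40 x 0.97) = 3.326 / 0.898 = 3.70
- Placebo: (0.60 x 0.95 x 5 + 0.40 x 0.97 x 2) / (0.60 x 0.95 + 0.40 x 0.97) = 3.626 / 0.958 = 3.79
- Spurious ratio: 3.70 / 3.79 = 0.98

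With 15% of women excluded in both arms the two expressions are identical and the ratio is 1.00. The 0.98 comes entirely from the assumed 10-point difference between arms.

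**4. PrEP infections expected in women.** Inputs: 1668 randomised, about 26 weeks on study PrEP, 10% loss of person-years, and placebo incidence and TDF/FTC effectiveness from Table 11, with the two drugs equally effective as section 9.3.2 assumes.

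- Person-years: 1668 x 0.90 x 26/52.18 = 748 over both arms.
- Rate on PrEP at 4 per 100 and 70% effectiveness: 4 x (1 - 0.70) = 1.2 per 100.
- Infections: 748 x 0.012 = 9.0 over both arms.
- In women, if their rate equals the overall rate: 9.0 x 0.50 = 4.5 to 9.0 x 0.80 = 7.2.
- At 65% women: 5.8. With an equal split, the 95% limits of the rate ratio lie a factor exp(1.96 x sqrt(4/5.8)), about 5, either side of the estimate.
- Lower extreme (3 per 100, 80% effective, 50% women): 748 x 0.006 x 0.50 = 2.2.
- Upper extreme (5 per 100, 50% effective, 80% women): 748 x 0.025 x 0.80 = 15.0.

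If women have a higher rate than men, their share of the infections rises. With 60% women at 5 per 100 before the 70% reduction, the count is 1668 x 0.60 x 0.45 x 0.015 = 6.8. In the central case the ceiling is the total of about 9.

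**5. How finely can the PrEP data be divided?** Three countries with two sites in Tanzania (section 6.11) imply at least four centres, so at least eight centre-by-gender strata for about 9 infections. At 80% women, men would have about 834 x 0.20 x 0.45 x 0.012 = 0.9 infections per arm.

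**The case against.** The strongest reply is that section 9.5 is only a summary and that adjustment sets and thresholds belong in the statistical analysis plan. That stands for anything the protocol leaves unsaid, including how the AIR handles strata. It does not dispose of the vaccine model, where the protocol states an adjustment that is narrower than its stratification. Nor does it remove the conditional wording for gender, which a later plan would inherit.

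A second reply is that the condition is sensible, because about six infections in women cannot settle effectiveness. This is right about precision: the limit is the number of events, not the wording. It is not a reason to let the decision to report depend on the observed count.

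Three stronger readings are tempting, and the document does not support them.

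- **That omitting gender biases vaccine efficacy.** A reader might infer this because pregnancy stops injections and affects only women participants. The rule applies in all three arms, and participants and assessors are blind to active versus placebo. Bias needs exclusions among women to differ between arms, and nothing in the protocol indicates that they would.
- **That the direct PrEP comparison is biased.** The only exclusion is HIV infection at enrolment, which precedes treatment. There is no selection after randomisation, so the stratified allocation protects the comparison.
- **That the PrEP rates and AIR should be stratified by centre and gender.** About 9 infections over at least eight strata would leave many strata with none or one, and AIR limits in men might not be estimable.

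**Conclusion.** The point holds as a mismatch between design and analysis for the vaccine, and as a poorly fixed reporting rule for PrEP. For the vaccine the size is negligible: at most about 0.2 points of power, no change to 556 per group or 1668 in total, and no demonstrated bias. This rests on the assumed follow-up, share of women and incidence ratios in the simulation, and the result was stable across the ranges tried.

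For PrEP the consequence is one of reporting, not validity. With roughly 4.5 to 7 infections expected in women in the central case, and about 2 to 15 across the protocol's own range of incidence and 50-80% effectiveness, the undefined condition could well be judged unmet. The share of women is an assumption throughout. Reporting by gender regardless of count will not give a firm answer for women. It ensures that whatever evidence exists is shown and that its appearance does not depend on a choice made after seeing the data.

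**What to change.** - **Section 9.5.1:** have the Cox model adjust for, or stratify by, gender as well as centre.
- **Section 9.5.2:** replace the conditional sentence with a commitment to report infections, person-years, rates and the rate ratio with exact limits separately for women and men whatever the count, labelled descriptive and imprecise. Give the AIR by gender only where it can be estimated. Say explicitly that these are separate results by gender and not one gender-adjusted estimate.

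The overall PrEP comparison can stay as it is.

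The cost is one sentence in each section. Gender is already recorded for randomisation, so no new data are needed, and the sample size does not change. The drawback is wide intervals that could be over-read, which is why the descriptive label should be part of the text. If no infections occur in one gender, the rate ratio has no usable limits, and the counts and rates alone should be shown.
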